##### **8.4.2.3 Enrolled Sample Acquisition and Analysis**

The customers' response on the "ease of use" is a qualitative and quantitative assessment of how quickly, easy and safely an instrument-naïve operator should be able to use the PEO/IUO BD FACSPresto System, after 3 hrs or less training period and the "anxiety" factor as to fear of breaking something or losing large amount of patient data without noticing it..

### **8.5 Acceptance Criteria**

#### **8.5.1 Primary Endpoint**

- For Abs CD4 count, the 95% confidence interval for the slope estimated using Deming Regression shall be within 0.9 to 1.1 when regressing the investigational device to the predicate device. The R2 from the Deming regression shall be  $\geq 0.9$ . The intercept estimated from the Deming Regression shall be within  $\pm 20$  counts.
- For %CD4, the 95% confidence interval for the slope estimated using Deming Regression shall be within 0.9 to 1.1 when regressing the investigational device to the predicate device. The R2 from the Deming regression shall be  $\geq 0.9$ . The intercept estimated from the Deming Regression shall be within  $\pm 3\%$ .

#### **8.5.2 Secondary Endpoints**

CD4 in capillary blood

- For Abs CD4 count in capillary blood, the 95% confidence interval for the slope estimated using Deming Regression shall be within 0.90 to 1.10 when regressing the investigational device to the predicate device. The R2 from the Deming regression shall be  $\geq 0.90$ . The intercept estimated from the Deming Regression shall be within  $\pm 20$  counts.
- For %CD4 in capillary blood, the 95% confidence interval for the slope estimated using Deming Regression shall be within 0.90 to 1.10 when regressing the investigational device to the

predicate device. The R2 from the Deming regression shall be  $\geq 0.90$ . The intercept estimated from the Deming Regression shall be within  $\pm 3\%$ .

#### **Hb in venous and capillary blood**

- For Hb, the the 95% confidence interval for the slope estimated using Deming Regression shall be within 0.9 to 1.1 when regressing the investigational device to the predicate device. The R2 from the Deming regression shall be  $\geq 0.9$ . The intercept estimated from the Deming Regression shall be within  $\pm 0.5$  g/dL.
- For capillary blood Hb concentration, the mean difference (bias) for samples with Hb concentration of  $10.5 \pm 1$  g/dL (clinical decision point) between the BD FACSPresto System result and the predicate system result shall be  $< 7\%$ , with  $> 95\%$  confidence, with respect to specimens typical in the target markets.

OR

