**Clinical decision points for Hb (only capillary blood)**

| Bins (g/dL) | Anticipated total | Minimum |
|--------------------|--------------------------|----------------|
| $4.5 \pm 1^*$      | 80                       | 40             |
| $10.5 \pm 1^*$     | 80                       | 40             |
| $17 \pm 1^*$       | 80                       | 40             |

\*FIO: For information only

To complete bin enrollment specifically for the Hb bins, up to 15% of the patient samples may be manipulated by diluting or spinning off plasma and then tested.

Only the BD MedLab will manipulate the venous blood samples for the Hb bins. If the minimum number of

specimens is not enrolled at each clinical decision point for Hb; the sites will be asked to use Hb controls to complete enrollment.

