##### **8.4.2.2 Evaluation of Hb concentration in venous and capillary blood**

Expected difference between the investigational system testing capillary blood specimens versus the predicate system using venous blood specimens measured as Hemoglobin concentration.

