### 8.7.2 Secondary Endpoints CD4 and Hb Binning

The secondary endpoint binning for AbsCD4 and %CD4 in capillary blood will apply the same bins described for CD4 in venous blood in section 8.7.1.

The secondary endpoints will address Hb bias determination between the investigation and predicate methods using venous blood. Additional bias analysis will be required around the clinical decision point of 10.5 (9.5-11.5) for determination of Hb in capillary blood using investigational versus the predicate method using venous blood. Three bins have been defined for Hb.

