#### Clinical Decision Points for HB (Only capillary blood)

| Bins (g/dL)                    | Total # Desired | Minimum   |
|--------------------------------|-----------------|-----------|
| <math>4.5 \pm 1</math>  | 60       | 40 |
| <math>10.5 \pm 1</math> | 60       | 40 |
| 17                      | 60       | 40 |

For each specimen, the mean differences between investigational and predicate results (for both Abs CD4 and %CD4), will be calculated and pooled across all specimens to produce a mean difference. Estimates from the Deming regression will be used to evaluate the equivalency between the investigational and predicate systems, according to the acceptance criteria presented in Section 8.5

It is anticipated that the total number of enrolled specimens will exceed 400 in order to achieve the required number of evaluable specimens in each age and CD4 bin.

For each Hb specimen, the mean differences between investigational and predicate results will be calculated and pooled across all specimens to produce a mean difference. Bias analysis at the clinical decision point of  $10.5 \pm 1$  will be used to evaluate the equivalency between the investigational and predicate systems, according to the acceptance criteria presented in Section 8.4. Additional analysis at  $4.5 \pm$  and  $17 \pm 1$  may be included for information only

Note that when the number of evaluable specimens reaches the desired target within each CD4 bin, data for any remaining specimens enrolled in that bin may be excluded from final data

analysis (see Data Evaluation for eligibility from Analysis in section 8. 2for details). BD will track bin enrollment during the course of the study and will notify sites when a target for any bin has been reached, so that sites can preferentially enroll specimens for other bins.

Ease of Use data will be discrete and qualitative variables obtained from small number of individuals at the participating clinical sites in the study. Data will be summarize and presented in tables or graphs. Additional statistical analysis is anticipated to be limited. Note that a subset of the total Accuracy data (i.e., from the site enrolling the most specimens) may be analyzed separately for the purpose of updating the technical file for CE declaration.

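### The capillary Hb acceptance rule at 10.5 ± 1 g/dL has no lower limit, is marked information-only elsewhere, and ends in an unfinished OR

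*Protocol*

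**What the plan says.** All references are to the protocol.

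- **Section 8.5.2, Hb in venous and capillary blood, second bullet.** "For capillary blood Hb concentration, the mean difference (bias) for samples with Hb concentration of" 10.5 ± 1 g/dL "between the BD FACSPresto System result and the predicate system result shall be" less than 7%, at more than 95% "confidence, with respect to specimens typical in the target markets". No absolute value or lower limit is given. The bullet is followed by the single word OR, and the next text is the heading of Section 8.6.
- **Section 8.5.2, same heading, first bullet.** For Hb, the 95% confidence interval of the Deming slope must lie within 0.9 to 1.1, R2 must be at least 0.9, and the intercept must be within ±0.5 g/dL. The bullet does not say whether it covers venous Hb, capillary Hb or both.
- **Section 4.1.6, table of capillary decision points.** The rows 4.5 ± 1, 10.5 ± 1 and 17 ± 1 all carry an asterisk, explained as "FIO: For information only".
- **Section 8.7.2, before the tables.** "Additional bias analysis will be required around the clinical decision point of 10.5 (9.5-11.5) for determination of Hb in capillary blood".
- **Section 8.7.2, after the tables.** The bias analysis at 10.5 ± 1 "will be used to evaluate the equivalency between the investigational and predicate systems, according to the acceptance criteria presented in Section 8.4". Only the analyses at 4.5 and 17 "may be included for information only".

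**The concern.** An acceptance criterion has to say what fails. This one limits over-reading by the device and sets no limit on under-reading, although Section 8.7.2 says its purpose is to judge equivalency. Every slope and intercept limit in Section 8.5 is two-sided.

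The status conflict adds a second problem. On Section 4.1.6 the result at 10.5 ± 1 decides nothing; on Sections 8.5.2 and 8.7.2 it decides capillary Hb. The unfinished OR leaves open whether there is another route to passing. Together these allow the capillary Hb verdict to be settled after the data are seen. Hb is one of the three quantities in the proposed intended use (Section 1.4), and the accuracy data are meant for the 510(k) submission (Section 1.3).

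**Working it through.** **There is no plan figure to reproduce.** The protocol gives no SD, power or derivation for the specimen numbers at 10.5 ± 1. The limit itself corresponds to 0.07 × 10.5 = 0.735 g/dL (0.665 at 9.5 and 0.805 at 11.5).

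**Step 1: the 7% rule alone.**
- *From the protocol:* limit 7%; n = 40 (minimum), 60 (target in 8.7.2), 80 (anticipated in 4.1.6).
- *Assumed:* SD of the paired percent difference of 3, 5, 7 or 10%; difference taken as a percentage of the predicate.
- *Rule as written:* mean + t × SD/√n < 7%.
- *Two-sided rule:* mean ± t × SD/√n lies wholly within -7% to +7%.

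Because the protocol does not state sidedness, both rules were simulated with one-sided 95% limits and with a two-sided 95% interval, 200,000 runs per setting. Pass probabilities over all n and SD were:

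| True bias | As written | Within ±7% |
|---|---|---|
| -15% | 100% | 0.0% |
| -10% | 100% | 0.0% |
| -7% | 100% | about 5% (one-sided limits) or 2.5% (two-sided interval) |
| 0% | 99% to 100% | 98% to 100% |
| +7% | about 5% or 2.5% | about 5% or 2.5% |

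The largest loss at zero bias is from 99.1% to 98.1% (n = 40, SD 10%, two-sided interval).

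**Step 2: both bullets together, taking the Deming bullet to cover capillary Hb.** If the device reads slope × predicate + intercept, the percent bias at 10.5 g/dL is

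(slope - 1) × 100 + 100 × intercept / 10.5.

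- Proportional -15%: the slope is 0.85, outside 0.9 to 1.1. The Deming bullet rejects it.
- Slope 0.93, intercept -0.45: 0.93 × 10.5 - 0.45 = 9.315 g/dL, and -1.185 / 10.5 = -11.3%. This meets both bullets if the slope interval is no wider than ±0.03 and R2 is met.
- Slope 0.91, intercept -0.50: -9.0 - 4.8 = -13.8%. This passes if the slope interval is no wider than ±0.01.
- Outer bound, slope 0.90, intercept -0.50: 8.95 g/dL, and -1.55 / 10.5 = -14.8%. It cannot quite be reached, because the whole slope interval must stay above 0.9.
- With the intercept at -0.50 (-4.8%), a slope of about 0.978 already gives -7%, since 7.0 - 4.8 = 2.2.

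Take the second case with n = 40 and SD 7%. The one-sided half-width is 1.86%, so the upper limit is -11.3 + 1.86 = -9.4%. This meets the signed rule, yet the whole interval is below -7%.

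**Step 3: status.** One section marks all three decision points information-only. Another keeps that label for 4.5 and 17 and uses 10.5 to judge equivalency. Both cannot apply. Section 8.4, which 8.7.2 cites for the criteria, defines endpoints; the criteria are in 8.5.

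**Step 4: duplicated tables.** The first Hb range-bin edge is 9 g/dL in 4.1.6 and 10 g/dL in 8.7.2. The targets are the same in both (140 + 180 + 80 = 400), as are the lower figures (90 + 100 + 60 = 250). The decision-point target is 80 in 4.1.6 and 60 in 8.7.2, with a minimum of 40 in both.

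**The case against.** **The authors probably meant absolute bias.** Section 8.7.2 speaks of equivalency, and a bias below 7% is common shorthand for size in either direction. That is plausible and makes the repair easy. It does not rescue the text, because an acceptance rule should not need its direction inferred.

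**The Deming bullet already guards against under-reading.** This largely stands. A reader might infer that a device reading Hb far too low would pass the trial, but the documents do not support that in general: a proportional -15% fails on slope. If the Deming bullet is venous-only, a device-wide under-read must still face it there, and only an under-read specific to capillary blood has no limit. What remains is the range between -7% and about -14%, which both bullets together can let through.

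**The bin tables do not feed this rule.** This stands. A reader might infer that the 10.5 rule rests on two conflicting Hb bin tables. Section 4.1.6 restricts the 9 v 10 g/dL range bins to venous blood, and no Hb acceptance criterion is applied bin by bin.

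**Section 8.4.2.2 does not omit venous Hb altogether.** A reader might infer that it does, because its one sentence reads "Expected difference between the investigational system testing capillary blood specimens versus the predicate system using venous blood specimens measured as Hemoglobin concentration". Its heading, the second secondary objective in Section 2.2 and the heading in 8.5.2 all name both specimen types, so this is a drafting gap.

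**Text after OR may have been lost.** This cannot be excluded, so the sponsor has to say what belongs there.

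**Conclusion.** The point holds for the capillary Hb criterion. As written it has no lower limit: alone, it passes true biases of -7%, -10% and -15% with probability 100% for n of 40 to 80 and assumed SDs of 3% to 10%. Combined with the Deming bullet, if that applies to capillary Hb, it can still pass a negative bias of more than 7%, up to about 14% at 10.5 g/dL. The 14% bound rests on a linear relation between the methods and a narrow slope interval. The contradictory status, the unfinished OR and the wrong cross-reference are plain on the page and need no assumption.

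This is a secondary endpoint; the primary CD4 criteria are not affected. The table differences are minor and separate: they affect enrolment, and the capillary pass/fail rule is the same under either table.

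**What to change.** Before analysis:

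1. In 8.5.2, state the limit as two-sided: the confidence interval of the mean percent difference at 10.5 ± 1 g/dL lies within -7% to +7%. State the confidence convention (one-sided 95% limits or a two-sided 95% interval).
2. In 4.1.6, remove the information-only mark from 10.5 ± 1, so that it agrees with 8.5.2 and 8.7.2. Leave it on 4.5 and 17.
3. Have the sponsor either complete the alternative after OR or delete the word.
4. State whether the Deming Hb criterion applies to venous Hb, capillary Hb or both. It should not be dropped for capillary Hb by default, since the heading covers both.
5. Correct the reference in 8.7.2 from Section 8.4 to Section 8.5.
6. Separately, reconcile the range-bin edge (9 v 10 g/dL) and the decision-point target (80 v 60) so that each table has one version.

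The cost is wording and a slightly harder criterion. At zero true bias the two-sided rule still passes 98% to 100% of the time over the range examined.

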### **8.6 Methods to Reduce Bias**

Blinding of diagnostic results from study personnel is facilitated by the de-linking process during study enrollment: study personnel who have access to subject information will not be involved in acquiring or analyzing specimens. The site personnel who will perform sample preparation and acquisition will have study-specific training to ensure consistent techniques to minimize bias.

### **8.7 Analysis Method for the Accuracy Evaluation Procedure**

For the study data generated at the sites, the minimum number of WB specimens that provide valid study results (i.e., meeting all inclusion criteria and protocol requirements) is 400 specimens. It is anticipated that the total number of enrolled specimens will exceed 400 to achieve the required number of evaluable specimen in each age, CD4 and Hb bins. The desired number for each CD4 and Hb bin is listed below:

#### **8.7.1 Primary Endpoint CD4 Binning**

**Abs CD4 Bins for Accuracy**

| Bins (cells/mL)              | Total # Desired | Minimum |
|-------------------------------------|------------------------|----------------|
| 1) $50 \leq \text{CD4} < 250$       | 100                    | 80             |
| 2) $250 \leq \text{CD4} < 500$      | 100                    | 80             |
| 3) $500 \leq \text{CD4} < 1000$     | 100                    | 80             |
| 4) $1000 \leq \text{CD4} \leq 5000$ | 100                    | 80             |

**%CD4 Bins for Accuracy**

| Bins (%CD4)                  | Total # Desired | Minimum |
|-------------------------------------|------------------------|----------------|
| 1) $5 \leq \text{CD4}\% < 20\%$     | 133                    | 110            |
| 2) $20 \leq \text{CD4}\% < 35\%$    | 134                    | 110            |
| 3) $35 \leq \text{CD4}\% \leq 65\%$ | 133                    | 110            |

### 8.7.2 Secondary Endpoints CD4 and Hb Binning

The secondary endpoint binning for AbsCD4 and %CD4 in capillary blood will apply the same bins described for CD4 in venous blood in section 8.7.1.

The secondary endpoints will address Hb bias determination between the investigation and predicate methods using venous blood. Additional bias analysis will be required around the clinical decision point of 10.5 (9.5-11.5) for determination of Hb in capillary blood using investigational versus the predicate method using venous blood. Three bins have been defined for Hb.

#### Hb Bins for Accuracy

| Bins (g/dL)                 | Total # Desired | Minimum |
|-----------------------------|-----------------|---------|
| 1) $2 \leq \text{Hb} < 10$  | 140             | 90      |
| 2) $10 \leq \text{Hb} < 13$ | 180             | 100     |
| 3) $13 \leq \text{Hb} < 20$ | 80              | 60      |

#### Clinical Decision Points for HB (Only capillary blood)

| Bins (g/dL)                    | Total # Desired | Minimum   |
|--------------------------------|-----------------|-----------|
| <math>4.5 \pm 1</math>  | 60       | 40 |
| <math>10.5 \pm 1</math> | 60       | 40 |
| 17                      | 60       | 40 |

For each specimen, the mean differences between investigational and predicate results (for both Abs CD4 and %CD4), will be calculated and pooled across all specimens to produce a mean difference. Estimates from the Deming regression will be used to evaluate the equivalency between the investigational and predicate systems, according to the acceptance criteria presented in Section 8.5

It is anticipated that the total number of enrolled specimens will exceed 400 in order to achieve the required number of evaluable specimens in each age and CD4 bin.

For each Hb specimen, the mean differences between investigational and predicate results will be calculated and pooled across all specimens to produce a mean difference. Bias analysis at the clinical decision point of  $10.5 \pm 1$  will be used to evaluate the equivalency between the investigational and predicate systems, according to the acceptance criteria presented in Section 8.4. Additional analysis at  $4.5 \pm$  and  $17 \pm 1$  may be included for information only

Note that when the number of evaluable specimens reaches the desired target within each CD4 bin, data for any remaining specimens enrolled in that bin may be excluded from final data

analysis (see Data Evaluation for eligibility from Analysis in section 8. 2for details). BD will track bin enrollment during the course of the study and will notify sites when a target for any bin has been reached, so that sites can preferentially enroll specimens for other bins.

Ease of Use data will be discrete and qualitative variables obtained from small number of individuals at the participating clinical sites in the study. Data will be summarize and presented in tables or graphs. Additional statistical analysis is anticipated to be limited. Note that a subset of the total Accuracy data (i.e., from the site enrolling the most specimens) may be analyzed separately for the purpose of updating the technical file for CE declaration.

## **8.8 Biostatistics Report**

A statistical report will be prepared by the biostatistician after data analysis is complete.

## **9.0 STUDY MATERIALS AND SUPPLIES**

### **9.1 Investigational Product Labeling**

The following products will be provided bearing “PEO/IUO” label/labeling indicating that they may only be used for performance evaluation purposes only:

The “PEO/IUO” instrument, reagents, controls, and software will be provided bearing labels/labeling indicating “PEO/IUO”. Additional information regarding system operation and reagent composition will be contained in Performance Evaluation only instructions for use and package inserts that will be provided to the site prior to or during study initiation.

Additional information regarding product composition, handling, etc. will be contained in a “PEO /IUO” package insert.

### **9.2 Study Products Shipment and Receipt**

BD will include appropriate shipping log(s) in all material shipments to the sites: Study Accountability Log(s) for PEO/IUO/IVD Instrument, Reagents, Software; and/or Miscellaneous Materials Shipment Log(s).

All “PEO/IUO” supplies for initial training will be labeled “Training only”. All “PEO/IUO” or IVD supplies for training and for the study will be verified upon delivery by site personnel and entered on the center's Study Accountability Logs. After receipt has been documented on Study Accountability logs, the log originals are retained by the site to allow for documentation of usage and final disposition of all investigational materials (i.e., used, unused and destroyed at the site, or unused and returned to BD).

### **9.3 Study Product Accountability**

The Sponsor will provide the Investigator with investigational product upon receipt of all necessary study documentation (i.e. IRB/IEC approval letter and approved clinical trial agreement).

- During the investigation, the Investigator is responsible for ensuring that: Only specimens that qualify for study enrollment are run on the IUO system;
- At the testing laboratory, all investigational products and devices are maintained under controlled access storage, and the use of investigational products are strictly controlled;

- **For the duration of the study**, any device or components that are removed from their packaging and not used are segregated from general use.

The Investigator is responsible for maintaining accurate accountability records for the use of investigational materials on the Study Accountability Logs. These records will be reviewed at all monitoring visits to ensure compliance, and will document:

- Receipt dates and quantity,
- Dates and quantity used, including identification of samples, and
- Amount used, discarded or returned.

Study Accountability Logs will be verified by the site monitor against the Shipping Logs.

## **9.4 Required Study Materials and Supplies**

### **9.4.1 Instrumentation**

If any of the following are not available at the site, required items will be provided by BD.

- BD FACSCalibur™ with FACS Loader
- BD FACStation workstation
- BD Multiset Software version 1.1 or later
- BD FACStation Software version 4.2 or later (includes FACSComp™ and Worklist Manager)
- PEO/IUO BD FACSPresto System instrument and accessories
- PEO/IUO BD FACSPresto Software 1.0
- Sysmex analyzer (KX-21)

### **9.4.2 Reagents, and Controls**

- BD Calibrite beads
- BD Tritest™ CD3/CD4/CD45 reagent
- BD Multicheck Process Controls (low or normal) or Lymphosure (Low and Normal) or CD-Chex Plus/Chex CD4 Low
- BD Trucount™ tubes
- BD FACS Lysing Solution
- BD FACSFlow for the FACSCalibur™
- PEO/IUO BD FACSPresto™ Reagent Kit (includes reagent PEO/IUO BD CD4/%CD4/Hb cartridges, lancets, alcohol swabs and transfer pipettes)
- Eurotrol 301 (Low, Normal and High)
- Sysmex reagents (SYSPK-30L; SYSSWH-200A)
- Sysmex L, N and H controls (three clinical sites; part number: SYS140-3004-0)

